#### Description of the comparator

Control classes will engage in standard school activities/routine lessons and will be provided the intervention in the beginning of the next school calendar year.

### Criteria for discontinuing or modifying allocated intervention/comparator {15b}

As the trial allocates intervention at the classroom level, discontinuation or modification of the allocated interventions in the trial may occur at the following levels:Individual student-level: A student may postpone or terminate active participation in the intervention if (a) excused by the teacher or school administration in accordance with the school’s policies or procedures or (b) severe safeguarding concerns related to the intervention as determined by the Trial Steering Committee (TSC)Class-level: An intervention class session may be postponed or terminated early due to (a) operational constraints such as emergency closures, strikes or staff shortages experienced by the school or (b) severe safeguarding concerns related to the intervention determined by the TSC

### Strategies to improve adherence to intervention/comparator {15c}

We will develop Standard Operating Procedures (SOPs) around consenting procedures, data collection and management and intervention delivery to ensure fidelity and adherence to the protocol. All implementation researchers will fill out session logs to introduce a standard monitoring framework for data quality.

Although we do not have any target tools to measure adherence and fidelity specifically, we will be monitoring fidelity and adherence to the intervention recording the number and content of each session using observation forms which will be filled out by researchers facilitating *Lina* lessons.

### Concomitant care permitted or prohibited during the trial {15d}

As this is taking place within routine classes in schools, students and teachers will continue to receive all usual educational and wellbeing support delivered by schools. Given the vulnerable status of young participants in the trial, they will not be excluded from accessing additional interventions during the trial period. Information on the use of any additional support services availed of by students as a result of the trial within schools will be captured through trial assessments (e.g. Health Economics Inventory forms) and reviewed in the analysis to assess the cost of delivering the intervention in the schools.

### Ancillary and post-trial care {34}

This trial has been identified as a low-risk, school-based psychosocial intervention so we do not anticipate participants would require ancillary or post-trial care. In the event that participants do require additional support, they will continue to have access to the usual educational and mental health support available within their schools and we will follow school safeguarding policies and procedures at all times. The study is covered under the University of Birmingham’s standard research indemnity scheme for participants.

### Outcomes {16}

The trials will collect information from participants on a range of mental health, social and economic evaluation-related outcomes including sense of belonging, symptoms of depression, social anxiety, loneliness, quality of life, stigma, social awareness and resource use.

#### Primary outcome

The primary outcome will be sense of belonging/class climate as measured by the Delaware School Climate Survey- Student (DSCS-S) measured post intervention (8–10 weeks) and at follow-up (6 months). This is a 23-item student-report scale to measure the sense of belonging an individual feels within a classroom context [15]. The scale is comprised of five subscales: Teacher-Student Relationships; Student–Student Relationships; School Safety; Fairness of the Rules and School Liking [16]. Items are rated on a Likert scale, with negatively worded items reverse-scored. Subscale scores for Teacher–Student Relationships, Student–Student Relationships, School Safety, Fairness of the Rules and School Liking are computed as the mean of their respective items. The overall school climate score is calculated as the mean of all 23 items and analysed as the mean difference in total or subscale scores between Lina and control groups from baseline and post-intervention scores (controlling for baseline score and clustering). The DSCS-S is justified for measuring this outcome as it demonstrates strong psychometric validity and reliability in Portugal [17], Anglophone contexts, e.g. USA [16], and in Eastern European settings, e.g. Serbia [18] along with widespread international use in low-resource settings. The wording of the items, in all three languages, has been adapted slightly to ask about the class climate, as opposed to the overall school climate. This is in order to make the measure sensitive to the climate of the specific classroom in which the intervention was delivered.

#### Secondary outcomes

In line with the developing *Lina* theory of change, secondary outcomes were selected to assess constructs anticipated to be affected by *Lina.* General wellbeing may be increased via increased belonging or other aspects associated with *Lina* such as exposure to the arts. Social anxiety and depression were selected as symptoms of mental distress that are both some of the most commonly experienced in adolescents, and (in the case of *social* anxiety) most likely to be positively impacted by *Lina*. Social awareness represents an area of psychological resources expected to be positively impacted by *Lina.* Loneliness is sometimes conceptualised as the counterpoint to belonging and is expected to be positively impacted by the positive class environment created by *Lina.* Finally, the *Lina* story touches directly on mental health issues in a way designed to reduce stigma. Measure selection was strongly influenced by availability of prior validation with young people in PT (where specific regulatory constraints exist around measures that can be used with young people in school settings), and by availability of data on sensitivity to change. Thus, the following student-report measures were selected. For all questionnaires, the total score (sum of all items) is the unit of analysis. For each outcome, the metric for analysis will be the mean difference in total or subscale scores between Lina and control groups at post-intervention, adjusted for baseline score and clustering via linear mixed methods models.WHO-5 Well-being Index is a 5-item measure of general well-being that has proven reliability and criterion validity among adolescents in the UK, Portugal and Czech Republic as part of a large cross-national validation study [19]. Scores are transformed to a score from 0 to 100, with lower scores indicating worse well-being [20].Patient Health Questionnaire-8 is an 8-item screening tool designed to assess the presence of depression symptoms [21]. PHQ-8 has strong equivalence with PHQ-9, has been tested for reliability and validity in 27 European countries—including the UK, Portugal and Czech Republic [22] and has demonstrated high internal consistency when administered with adolescents from vulnerable settings [23]. The total score can range from 0–24, with a score of ≥ 10 indicative of clinical-level depression [21].Social Anxiety Scale for Adolescents (SAS-A) is an 18-item questionnaire measuring adolescents’ social anxiety experiences in the context of peer relations [24] SAS-A has proven reliability and validity for Portuguese adolescents [25] and has been used in school-based screening of adolescents across France and Spain [26–28] with acceptable internal consistencies and validity. It contains three subscales: Fear of Negative Evaluation, Social Avoidance and Distress-New and Social Avoidance and Distress-General. Total score ranges from 0 to 90 with a higher score indicating a higher level of social anxiety [24].The 4-item University of California Los Angeles (UCLA) Loneliness Scale is a revised and shorter version of the full UCLA tool (20 items) [29]. The full UCLA scale demonstrated modest internal consistency in the assessment of loneliness in children and adolescents [30]. This version of the UCLA has been recommended by the Office of National Statistics in the UK [30, 31] as a strong measure of loneliness in youth aged 10–15 years, following adaptations. The tool has been translated and validated in Portugal and Slovakia with a modest internal consistency [32, 33].Social-Emotional Learning Edition of the Strengths and Difficulties Inventory System [brief version] (SSIS SELb) Social Awareness subscale is a 4-item assessment that evaluates the social-emotional skills of children and adolescents in relation to their social awareness. It measures how much students take into account others’ point of view, particularly those from different backgrounds [34]. SSIS SELb was translated and validated for use among school-going adolescents in 6 European countries including Portugal with a strong measurement for reliability and structural validity, supporting its use for international research with appropriate adaptation and translation [34].Peer Mental Health Stigmatisation Scale-Revised (PMHSS-R) Stigma Awareness subscale is 5-item assessment of individually held stigmatising beliefs. It is answered on a 5-point Likert scale of agreement [35]. PMHSS-R has been developed in Ireland [35] and validated in European contexts (Spain) [36] but there is no country-specific validation for the UK, Portugal and Czech Republic. However, at the time of drafting this protocol, PMHSS-R is currently the only validated tool that assesses both awareness and agreement of stigma and was considered justified in use for measuring these outcomes in the trial.EQ-5D-Y-3L is a child-friendly questionnaire to describe young peoples’ health across five dimensions: Mobility; Looking After Myself; Doing Usual Activities; Having Pain or Discomfort; and Feeling Worried, Sad or Unhappy [37]. Each dimension has three levels of response. The tool has been translated in Czech [38] and Portuguese [39] and demonstrates strong psychometric evidence for validity and reliability with adolescents in the UK [40] and among Portuguese speakers [39].Child Health Utility-9D (CHU-9D) is a self-report measure of health-related quality of life suitable for 7- to 17-year-olds. It consists of 9 dimensions each measuring a different domain (worried, sad, pain, tired, annoyed, schoolwork, sleep, daily routine and activities). Each domain has 5 levels of severity. The CHU-9D has been locally translated for administration among young people in Portugal, Czech Republic [41] and the UK and demonstrated modest internal consistency and validity among children, adolescents and young adults within the UK and Portuguese speakers [39].

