## Statistical methods

### Statistical methods for primary and secondary outcomes {27a}

#### Statistical analysis

Data for the three trials will be analysed separately (by country), before later being pooled for overall analysis.

Participant level socio-demographic data and cluster level (classroom) data will be summarised at baseline for both arms of the trial.

The primary outcome is the Delaware Class Climate score at the end of *Lina* delivery (8–10 weeks post baseline and follow-up). This will be compared between *Lina* and control groups using a linear mixed effects model with a random effect for classroom and school, allowing for the clustering of children, within classes, and within schools. The model will include baseline level of the Delaware Class Climate as a covariate, as well as demographics (that are known to affect outcome). The analysis will use intention to treat by including all participants in the arm to which they were randomised, whether or not they completed the *Lina* programme and including all students in the analysis by using multiple imputation. We will set out in the statistical analysis plan (SAP) how missing data will be handled, including planned sensitivity analyses.

Secondary outcomes are WHO-5, PHQ-8, SAS-A, UCLA Loneliness Scale, SSIS SELb, PMHSS-R, EQ-5D-Y-3L and CHU-9D all measured at post-intervention (T1) and 6 months post baseline (T2). Each variable will be analysed using a generalised linear mixed effects model with a link function appropriate to the outcome distribution, with random effects for classroom and school. All models will include the baseline value of the outcome.

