#### Economic evaluation

We will conduct an economic evaluation alongside the three trials aiming to assess the cost effectiveness of Lina in comparison with usual lessons from a school perspective. The time horizon for the evaluation will be from the point of randomisation until the 6-month follow-up. Intention-to-treat analysis will be applied.

The primary outcome for our economic evaluation is the Quality Adjusted Life Years (QALYs), to be converted from the CHU-9D data by applying for the UK tariff [47]. Secondary outcomes include the EQ-5D-Y-3L and the Delaware Class Climate score. The outcomes data will be collected at baseline, post-intervention, and 6 months follow-up using the e-CRFs.

Resource use includes three groups, i.e. (1) time spent by teachers/psychologists on preparing and delivering *Lina* and usual sessions as well as other professionals’ time spent on delivering *Lina* and usual sessions, (2) resource use for providing necessary equipment to deliver Lina sessions and (3) time spent by teachers/psychologists and other professionals on providing additional support to students as well as managing students’ disruptive behaviours. We will collect relevant unit cost data to convert the quantity of resource use for each item to monetary values. The cost for resource use will be presented at student and time point level (i.e. baseline, immediately after intervention and 6 months follow-up). We will explore the appropriate approach to handle missing values in costs and outcome data. No discounting will be required for costs and outcomes data.

A cost-utility analysis will be performed on each country’s data to estimate the incremental costs of *Lina* compared to usual lessons per additional QALY gained (or the Incremental Cost-Effectiveness Ratio (ICER)). We will report the uncertainties around the point estimate of the ICER. Also, the point estimate will be compared against the country-specific willingness-to-pay threshold(s). We will pool data from the three countries together to conduct a multiple-country cost-utility analysis. A few sensitivity analyses will be performed including (1) using the EQ-5D-Y-3L and the Delaware Class Climate score as outcome measures (2) conducting economic evaluation under alternative scenarios related to implementation (e.g. frequency of session delivery) to help contextualise the findings for future implementation (3) applying for alternative approach(es) to handle missing values.

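### The sum-of-items scoring rule for secondary questionnaires also covers EQ-5D-Y-3L and CHU-9D, giving unweighted severity counts and, for CHU-9D, a score inconsistent with the tariff used in the economic evaluation

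*Protocol article*

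**What the plan says.** Four parts of the protocol article bear on this.

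- **Outcomes {16}, Secondary outcomes, scoring rule.** "For all questionnaires, the total score (sum of all items) is the unit of analysis". The next sentence ties the score to the analysis: "For each outcome, the metric for analysis will be the mean difference in total or subscale scores between Lina and control groups at post-intervention". The list of measures follows directly and contains no exemption.
- **Same section, the two instruments.** "EQ-5D-Y-3L is a child-friendly questionnaire to describe young peoples’ health across five dimensions", and "Each dimension has three levels of response". Of CHU-9D: "It consists of 9 dimensions each measuring a different domain", and "Each domain has 5 levels of severity". Neither entry names a total, a subscale or an index.
- **Statistical methods {27a}, Statistical analysis.** The list of secondary outcomes ends "PMHSS-R, EQ-5D-Y-3L and CHU-9D all measured at post-intervention (T1" and goes on to add the six-month time point. Each outcome gets a generalised linear mixed model adjusted for its baseline value. The link function is left to suit the distribution. No score other than the item sum is given.
- **Statistical methods {27a}, Economic evaluation.** QALYs are the primary economic outcome, "to be converted from the CHU-9D data by applying for the UK tariff". EQ-5D-Y-3L is a secondary economic outcome and appears in a sensitivity analysis, with no scoring stated there. A separate Health Economic Analysis Plan is to be signed off before that work starts.

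**The concern.** A sum is a natural score when items are repeated indicators of one construct, as in a depression or social anxiety scale. EQ-5D-Y-3L and CHU-9D are built differently. Each asks one question per domain, and the domains are unlike: mobility and worry in one, pain and schoolwork in the other. Adding the level numbers treats one step in any domain as worth the same as one step in any other. A tariff exists to replace that equal weighting with preference weights.

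As written, an analyst who follows the protocol would report the arm difference for both instruments in units of summed levels. If levels are coded by severity, a higher sum means worse health, whereas a higher utility means better health. For CHU-9D, the effectiveness paper and the economic paper would then carry two treatment effects from the same answers, on different weightings, with no rule on which one represents quality of life.

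**Working it through.** **1. The plan's own figure, to settle scope.** The only power figure concerns the primary outcome. Inputs from Sample size {19}: d = 0.4, ICC 0.1, 18 analysable students per class, 40 classes, 720 per country (360 per arm). Two-sided alpha of 0.05 is assumed.

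- Design effect = 1 + (18 − 1) × 0.1 = 2.7.
- Effective number per arm = 360 / 2.7 = 133.3.
- Power = 0.904, which reproduces the stated 90%.

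The scoring of the two instruments does not enter this calculation.

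**2. Does the rule reach the two instruments?** The rule is universal in its wording and introduces the list that contains both. The following sentence allows a subscale in place of a total, but no subscale is named for either instrument, so this offers no other score. The Statistical analysis section leaves the link function open, not the score. On the text, both would be modelled as item sums.

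**3. What an item sum keeps.** Assume levels coded 1 to 5 (CHU-9D) and 1 to 3 (EQ-5D-Y-3L).

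| Instrument | Health states | Possible sums | Most states sharing one sum |
|---|---|---|---|
| CHU-9D | 5^9 = 1,953,125 | 9 to 45, i.e. 9 × 4 + 1 = 37 | 180,325 (sum 27) |
| EQ-5D-Y-3L | 3^5 = 243 | 5 to 15, i.e. 5 × 2 + 1 = 11 | 51 (sum 10) |

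A tariff that weights domains or levels unequally therefore cannot be recovered from the sum. The table shows only that. It does not measure bias.

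**4. How the two CHU-9D scores can differ.** Suppose, for illustration, an additive tariff in which one level costs *a* in domain A and *b* in domain B. No tariff values are in the documents, so these stay as symbols.

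- A student improves one level in A and worsens one level in B. Change in sum = −1 + 1 = 0. Change in utility = *a* − *b*, which is zero only if *a* = *b*.
- A student improves two levels in A and worsens one in B. Change in sum = −2 + 1 = −1, an improvement. Change in utility = 2*a* − *b*, a loss whenever *b* > 2*a*.

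Disagreement is therefore possible in principle. Whether it would be material in this trial cannot be computed from the documents.

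**5. The two CHU-9D derivations side by side.** Secondary outcomes and Statistical analysis: item sum, compared between arms in a mixed model. Economic evaluation: UK tariff applied to the same responses. Nothing in the article links the two or gives one precedence.

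**The case against.** The strongest reply is that the two CHU-9D scores serve different purposes. An unweighted summary in the effectiveness model and a tariff utility in the economic model can both be computed from the same items. That is true. It does not make the sum a suitable quality-of-life score, and the blanket sentence gives no sign that the two instruments were meant to be scored this way.

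Several stronger readings are tempting, and the documents do not support them.

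- **That QALYs will be built from item sums.** They will not. The economic evaluation applies the UK tariff to CHU-9D.
- **That the EQ-5D-Y-3L sensitivity analysis is unworkable because a sum cannot yield QALYs.** The sum rule is tied to the arm comparison in the mixed models, not to the economic evaluation. A value set may be named in the Health Economic Analysis Plan, which is not shown. The same sensitivity item also uses the Delaware score, which gives no QALYs, so the item is not confined to QALY outcomes.
- **That WHO-5 is contradicted.** Its own entry states the 0 to 100 scale and so qualifies the general sentence. If the transformation is a linear rescaling, tests and standardised effects do not change.
- **That the collapse of states measures the harm.** Any summed scale collapses response patterns. PHQ-8, with eight items and a total of 0 to 24, allows 24 / 8 = 3 points per item if items are scored alike, hence 4^8 = 65,536 patterns on 25 totals, and nobody objects to its sum. The objection here is equal weighting across unlike domains.
- **That the CHU-9D effects will have opposite signs.** Opposite coding is a matter of presentation. A true reversal of benefit is possible but not shown.

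**Conclusion.** The point holds as a modest defect in a stated rule. The scoring sentence covers two instruments for which it is unsuitable, and for CHU-9D it is inconsistent with the tariff the protocol uses elsewhere. It is a rule that has been fixed badly, not detail left to a later plan.

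It touches two of eight secondary outcomes. The primary outcome, the sample size, the planned QALY calculation and the data collection stand as they are. No numerical bias can be given.

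The conclusion rests on reading the sentence as it is worded, covering every measure in the secondary list. The counts assume consecutive integer coding of levels. The remark on direction assumes coding by severity. The possible disagreement between sum and utility assumes a tariff with unequal weights.

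**What to change.** In Secondary outcomes, and in the SAP before database lock:

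1. Limit the sum rule to the psychometric scales.
2. State that CHU-9D as a secondary outcome is analysed at T1 and T2 as the same UK-tariff utility that the economic evaluation uses.
3. State that EQ-5D-Y-3L is analysed as an index from a value set named before database lock. If no value set is adopted, report the distribution of levels in each dimension by arm.
4. As a minor clarification, state that WHO-5 is analysed on its 0 to 100 scale.

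The cost is wording only, recorded through the usual amendment route. The item responses are already collected, so no new data are needed and the sample size does not change.

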
#### Resource use data

We will collect three groups of data for resource use in the economic evaluation.First, we will collect data from teachers/psychologists on their time spent preparing and delivering *Lina* and usual sessions. The data will be collected for three periods, i.e. at baseline (with 3 months recall), the end of 8–10 weeks intervention (with 8–10 weeks recall for control group and weekly data collection for intervention group after each *Lina* session), and 6 months follow-up (with 6 months recall). In addition to time spent by teachers/psychologists, we will also collect data on other professionals’ time spent (e.g. administrative staff, teaching assistants) on delivering *Lina* or usual sessions. We developed four Health Economics Inventory forms for data collection on time spent by teachers/psychologists and other professionals.Second, our research team will collect data on the quantity and costs of equipment used for delivering *Lina* sessions, including smartphones, routers, headphones, and paper-based materials.Third, we will collect data on time spent by teachers/psychologists and other professionals (e.g. administrative staff, teaching assistants, counsellors) providing additional mental health/wellbeing support to students as well as managing students’ disruptive behaviours. The data will be extracted from school records for the period from 3 months before baseline till the end of 6 months follow-up.

